#### Natural conceptions and pregnancy outcome

Natural pregnancy, ongoing pregnancy, and live birth will be recorded by our team research nurse for a 2-year follow-up after the participant finishes 90 days of drug taking.

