**Methods:**

This study is a double-blinded, randomized placebo-controlled trial conducted in a public hospital in Hong Kong. Participants will be randomized, using computer-generated random numbers, with a 1:1 ratio to either the Wuzi Yanzong pill formula group or the placebo group. Both groups will be administered the drugs for 12 weeks. Participants will have a total of four visits for their semen and blood assessments for a 6-month period, and we will follow up for another 6 months to record their conception outcome. The primary outcome is to compare the total motile sperm count, natural conception rate, and pregnancy outcome to those under placebo treatment. Secondary objectives are sperm functions and assisted reproductive technology outcome.

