#### Study process

A semen analysis will be performed for patients in our andrology unit. If the TMS count is less than 20 million per ejaculate, our reproductive medicine practitioner will exam the inclusion and exclusion criteria and consent the patient. After recruitment, the patients are assigned randomly by the TCM team and are divided into the control group taking the placebo and the treatment group taking the WZYZ formula twice a day regularly for a period of 3 months. Semen samples will be taken at the baseline (week 0) and at 6 weeks and 12 weeks to determine if the semen quality has been improved by the formula. An additional semen analysis will be performed 3 months after completion of the treatment. Natural conception and pregnancy outcome will be followed up by our clinical nurse for another 6 months. Compliance will be recorded in the patient diary and by the research nurse via weekly phone calls (90 days of treatment). Patients with less than 63 days of treatment intake will be excluded; the incomplete intake will be considered as failure of compliance too. If the total compliance is less than 70%, then the patient will be considered to have dropped out of the study. The flow chart and study schedule are shown in Fig. 1 and Table 1, respectively. Part of the semen sample will be cryopreserved and separately stored in a − 80 °C freezer for a DNA fragmentation test and other sperm function tests, which will be explained in the “Outcome measurements” sections. A blood sample will also be taken concurrently with the semen samples for hormonal level examination, including routine follicle-stimulating hormone (FSH) and free androgen concentrations.

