**Fig. 1 Fig1:**
[figure not shown]
Study flow chart

**Table 1 Tab1:** Schedule of the study process

Time duration Time point	Study period								
	Recruitment by reproductive practitioner	Allocation by TCM team	Post allocation						
	1st visit	0 week	1–6 weeks	2nd visit^a^	7–12 weeks	3rd visit^a^	3–6 months	4th visit^a^	6–12 months
Enrollment:									
Eligibility screen	X								
Informed consent	X								
Allocation		X							
Interventions									
Administration of investigational product			X		X				
Assessments									
Semen analyses		X		X		X		X	
Blood tests		X				X			
Sperm DNA fragmentation		X		X		X		X	
Sperm cryotolerance		X		X		X		X	
Endocrine-disrupting chemicals test		X		X		X		X	
DNA maturity assay		X		X		X		X	
Liver and renal function assessment		X				X			
Natural conception and pregnancy outcome^b^									X

^a^ The 2nd through 4th visits are scheduled at the end of the time duration

^b^ Natural conception and pregnancy outcome are recorded by phone follow-up

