### Outcome measurements

The primary outcome is to compare the TMS count, natural conception rate, pregnancy outcome, and live birth rate. Secondary objectives are sperm functions and assisted reproductive technology (ART) outcome as well as the safety assessment on the TCM formula.

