#### ART outcomes

The ART outcomes include fertilization rate, embryo quality, blastocyst rate, implantation rate, and pregnancy rate. These data will be recorded in the treatment record if the patient receives ART in our hospital. If the patient receives ART elsewhere, the outcomes will be recorded by our team research nurse during a 2-year follow-up.

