### Trial status

This trial is at Version 1.3, 16/10/2018 (ChiTR). The actual study start date was 27/02/2018; the anticipated study end date is 31/01/2022. The recruitment start date was 27/02/2018; the anticipated recruitment end date is 31/01/2020.

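### Follow-up for the primary conception and pregnancy outcomes ends at month 12 in three places but 2 years after treatment in a fourth, and the 2-year version overruns the stated study end

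*Protocol article*

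**What the plan says.** All references are to the protocol article.

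- **Which outcomes are primary.** Outcome measurements states: "The primary outcome is to compare the TMS count, natural conception rate, pregnancy outcome, and live birth rate". Three of these four depend on how long couples are followed.
- **Month 12, three times.** The abstract describes four visits over 6 months and adds "we will follow up for another 6 months to record their conception outcome". Study process, after describing the semen analysis 3 months after treatment, says "Natural conception and pregnancy outcome will be followed up by our clinical nurse for another 6 months". Table 1 has a single mark for this outcome, in its last column (6–12 months), with the footnote "Natural conception and pregnancy outcome are recorded by phone follow-up".
- **Two years, once.** The subsection Natural conceptions and pregnancy outcome says of natural pregnancy, ongoing pregnancy and live birth that these events "will be recorded by our team research nurse for a 2-year follow-up after the participant finishes 90 days of drug taking".
- **Calendar.** Trial status gives recruitment from 27/02/2018 to an anticipated 31/01/2020, and "the anticipated study end date is 31/01/2022".
- **A secondary outcome, for context.** For men who receive assisted reproduction elsewhere, the ART outcomes subsection says "the outcomes will be recorded by our team research nurse during a 2-year follow-up".

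**The concern.** The same primary outcomes have two follow-up lengths in current text, and no sentence chooses between them or assigns them to different events. Two analysts could each follow the document faithfully and report different conception and live-birth rates. If the choice is left until outcomes are known, it also becomes a source of bias.

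Each version has its own difficulty. The short one leaves too little time for most conceptions to end in a birth, although live birth rate is a primary outcome. The long one does not fit the dates under Trial status.

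**Working it through.** **Inputs from the document:** 90 days of treatment; last enrolment 31/01/2020; first enrolment 27/02/2018; study end 31/01/2022; follow-up either to month 12 or for 2 years after the 90 days.

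**Assumed, because the document does not give it:** 38 weeks from conception to birth, with a range of 35 to 40 weeks. One month is taken as 30.4375 days.

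**1. Does either schedule reproduce the stated end date?**
- 2-year version: 31/01/2020 + 90 days = 30/04/2020; + 2 years = 30/04/2022. This is 89 days after 31/01/2022.
- Month-12 version: 31/01/2020 + 12 months = 31/01/2021. This is 365 days before 31/01/2022.
- The stated end equals last enrolment plus exactly 2 years. It omits the 90 treatment days that the 2-year wording places before its clock starts.

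**2. Who loses follow-up under the 2-year version?**
- Latest enrolment that still allows the full period: 31/01/2022 − 2 years − 90 days = 02/11/2019.
- Recruitment days after that date: 90 of 703. Under uniform accrual, 90/703 = 12.8% of participants.
- The loss ranges from almost nothing to 89 days per man.

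**3. Which conceptions can reach a term birth by month 12?** Latest conception month = 12 − (weeks × 7 / 30.4375).
- 35 weeks: 12 − 8.05 = month 3.95
- 38 weeks: 12 − 8.74 = month 3.26
- 40 weeks: 12 − 9.20 = month 2.80

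At 38 weeks, a conception in the last 8.74 of the 12 months (73%; 67% to 77% over the range) cannot end in a term birth before follow-up closes. The 6–12 month column of Table 1 spans about 26 weeks, less than the 35 to 40 weeks needed. A conception arising in it therefore cannot reach term birth within it.

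**4. The 2-year version has a milder form of the same limit.** 24 − 8.74 = 15.3 months after treatment (16.0 at 35 weeks). Later conceptions would not reach term birth by the end of the 2 years.

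**5. Illustration of what the choice does to the conception rate.** The document gives no monthly conception rate. Assume a constant 1% to 3% per month, counted from randomisation, with cumulative proportion 1 − (1 − h)^m.
- 12 months: 1 − 0.99^12 = 11%; 1 − 0.97^12 = 31%
- 27 months (3 of treatment + 24): 1 − 0.99^27 = 24%; 1 − 0.97^27 = 56%

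On these assumptions the two schedules differ by about a factor of two.

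**The case against.** Several arguments on the other side stand and limit the point.

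- **Conceptions during treatment.** A reader might infer that these, and those in months 3 to 6, are never counted, because the 2-year clock starts after day 90 and Table 1 is marked only from month 6. The text does not say this. The mark shows when phone recording takes place, and a call then can record an earlier pregnancy. Men are also contacted weekly during treatment and seen at weeks 6 and 12 and at month 6. What stands is that the start of counting is not stated.
- **A live-birth rate near zero by construction.** This follows only if conceptions before month 6 are excluded, which no section does. A conception in week 8 would deliver at about week 46 (8 + 38), inside month 12. Very preterm births are a further exception.
- **Live birth is not named in the 6-month passages.** They speak of conception and pregnancy outcome; only the 2-year subsection gives live birth a window. One could therefore read 6 months for conception and 2 years for birth. That does not work, because the 2-year sentence covers natural pregnancy as well.
- **A contrast of 6–17% against 21–52% conceiving.** Comparing 6 months of exposure with 24, at the same assumed monthly rates, again presumes that earlier conceptions are dropped. Counted from randomisation, the contrast is the smaller one shown in the working.
- **Power.** The sample size section sizes the trial on total motile sperm count alone, so no stated power figure changes.
- **The overrun is small and the dates are anticipated.** About 13% of men lose about 45 days on average out of 730, or roughly 0.8% of planned follow-up (0.128 × 45/730). If recruitment had taken the 12 to 18 months given under Sample size calculation, 2-year follow-up would end between 28/05/2021 and 25/11/2021, inside the stated end. The overrun rests on the Trial status dates.

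**Conclusion.** The contradiction is real and is wrong as written: month 12 in three places and 2 years after treatment in a fourth, for outcomes the protocol calls primary. It needs no assumption beyond reading the text.

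Its consequences depend on which version applies:

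- **Month 12.** The live-birth rate would omit term births from conceptions after about month 3.3 (2.8 to 4.0). This rests on the assumed 35 to 40 weeks from conception to birth.
- **2 years.** Follow-up of the last man ends 89 days after the stated study end. About 13% of participants are affected, by at most about 3 months. This rests on the Trial status dates and uniform accrual.

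Of these, the undefined window matters most; the calendar overrun is a minor consequence. The document does not support the further claims that treatment-period conceptions are excluded or that live births would be almost absent.

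**What to change.** Put one rule in the abstract, Study process, Table 1 and the subsection on natural conceptions. It should count natural conceptions from randomisation to a single stated cut-off, follow each counted conception to its end (loss or live birth), and carry a study end date that covers this. Either cut-off is workable:

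- **Keep 2 years after treatment.** Correct the abstract, Study process and Table 1, and move the end date to at least 30/04/2022 plus time for pregnancies conceived by then. At 38 weeks (266 days) that is about 21/01/2023.
- **Close conception counting at month 12.** Correct the 2-year subsection and follow counted pregnancies to delivery. For the last man, 31/01/2021 + 266 days = 24/10/2021, inside the current end date.

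The choice is the sponsor's, and should be made without sight of outcomes by arm. The ART outcomes subsection concerns a secondary outcome and does not conflict with the 6-month passages, so it need not carry this rule.

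The cost is an amendment and some later phone calls to couples who conceive; the first option also lengthens the study. Neither needs more visits or participants, since phone follow-up is already planned.

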### Sample size calculation

Our andrology unit conducted 892 semen analyses in 2017, in which 273 patients were diagnosed with oligoasthenospermia, and the mean of the TMS count of all patients failed to fulfill WHO criteria (5th edition, < 20 million per ejaculate) is 8.08 ± 6.19 million TMS. To detect 100% (double the TMS) improvement by the WZYZ TCM formula and accepting a type I error of 0.05 and a type II error of 0.2, the number of subjects to be recruited into each arm to detect a significant difference is 115 on each arm (Medcalc®, Version 15.6.1). To allow for a dropout/non-compliance rate of 20%, the number of subjects required in each arm is therefore 181, and the total number of subjects required in the study is 286. Therefore, the whole recruitment takes approximately 12–18 months to finish.

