### Data analysis

All the data are reported as percentages for nominal data or means ± standard deviation (SD) for continuous data. Patients with less than 70% compliance (i.e., out of 90 days treatment taking the WZYZ formula, less than 63 days of treatment completed) will be excluded. They will be considered as having dropped out and will not be included in the final analysis, but will be included in the intention-totreat analysis. The compliance will be checked by our research staff based on the patient diary and phone calls every 2 weeks. For non-compliance and missing outcomes, we will use two sets of analyses. The full analysis set (FAS) will include all patients who are randomized and will be conducted according to the intention-to-treat principle. The per protocol set will include all patients of the FAS who complete follow-up and do not have serious protocol violations.

For the baseline comparison, the independent Student *t* test or the Mann-Whitney *U* test is used to evaluate the mean or median differences between the placebo and intervention groups for continuous data depending on whether the data are normally distributed, and the chi-squared test is used for frequency comparison. For longitudinal data with a baseline, we will use repeated measures analysis of covariance (ANCOVA) to evaluate the mean difference between and within groups. All the tests are two-tailed, and the significance level is defined as a value of < 0.05.

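### The protocol contradicts itself on whether, and from when, men who stop treatment early are followed for conception and live birth, although the full analysis set must include them

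*Protocol article*

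**What the plan says.** The protocol article addresses this point in five places.

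- **Outcome measurements:** "The primary outcome is to compare the TMS count, natural conception rate, pregnancy outcome, and live birth rate".
- **Natural conceptions and pregnancy outcome:** natural pregnancy, ongoing pregnancy and live birth are recorded "for a 2-year follow-up after the participant finishes 90 days of drug taking".
- **Study process:** "Natural conception and pregnancy outcome will be followed up by our clinical nurse for another 6 months". This follows the semen analysis three months after treatment. The same section says: "If the total compliance is less than 70%, then the patient will be considered to have dropped out of the study".
- **Table 1:** the outcome is marked in the 6–12 month column, and note b reads "Natural conception and pregnancy outcome are recorded by phone follow-up". No completion condition is attached. The abstract describes the same schedule.
- **Data analysis:** men below 70% compliance are left out of the final analysis but kept in the intention-to-treat analysis. "The full analysis set (FAS) will include all patients who are randomized and will be conducted according to the intention-to-treat principle". The section also says: "For non-compliance and missing outcomes, we will use two sets of analyses".

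**The concern.** The follow-up clock in the outcome section starts at an event that occurs after randomisation and that some men will not reach. A man who stops in week 4 has no start date under that sentence, and the study process labels him a dropout from the study, not only from treatment. The full analysis set nevertheless needs his outcome. Naming two analysis sets does not close the gap, because a set says who is counted, not what is known about him.

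If staff follow the completion-based sentence, the conception and live-birth rates will be rates among finishers. Finishing could differ by arm, for example through adverse reactions, lack of perceived benefit or a move to assisted reproduction. The comparison would then lose the protection of randomisation on primary outcomes. No later analysis plan can recover outcomes that were never collected.

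**Working it through.** **1. The follow-up statements side by side**

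| Place | Outcomes named | Start | Length | Needs completion? |
|---|---|---|---|---|
| Natural conceptions and pregnancy outcome | natural pregnancy, ongoing pregnancy, live birth | finishing 90 days of drug | 2 years | yes, read literally |
| Study process | natural conception, pregnancy outcome | after the 3-month post-treatment semen analysis | 6 months | not stated |
| Table 1 | natural conception, pregnancy outcome | month 6 | to month 12 | no |

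The rows disagree on start, length and who is covered. Live birth is named only in the first.

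**2. Can the calendar window serve for live birth?** Assume about 9 months from conception to birth (not a figure in the protocol). A birth by month 12 needs conception by month 12 − 9 = 3, roughly the end of treatment. If conceptions were spread evenly over 12 months, at most 3/12 = 25% would have delivered by then. None of those conceived in months 6 to 12 would have. The 2-year clock ends at about month 3 + 24 = 27 and covers births from conceptions up to about month 18. Live birth therefore depends on the completion-based sentence.

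**3. How many men.** Inputs from the sample size section are 115 per arm, a 20% allowance for dropout or non-compliance, and a stated total of 286. Reproducing the total: 115/0.8 = 143.75, so 144 per arm and 288 in all, close to 286 = 2 × 143. The stated 181 per arm would give 362 and does not fit; that is a separate matter. Using 286:

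- 0.20 × 286 = 57.2 men in total, and 0.20 × 143 = 28.6 per arm.
- If all were unobserved, extreme values could move the difference in rates by ±28.6/143 = ±20 percentage points.

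The 20% pools dropout with non-compliance, and a non-complier can still be phoned, so 57 is an upper figure under that allowance.

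**4. Bias of a finishers-only comparison.** The protocol gives no conception rate and no arm-specific dropout, so these inputs are assumptions: no true effect, 20% conception in each arm, 143 men per arm, finishing share f, and non-finishers conceiving at k times the finishers' rate. Then

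finishers' rate = 0.20 / (f + (1 − f)k).

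| Finishing share, arm 1 / arm 2 | k | Finishers' rates | Bias (points) | Type I error (simulated, nominal 5%) |
|---|---|---|---|---|
| 90% / 70% | 0 | 22.2% v 28.6% | 6.3 | 19.9% |
| 90% / 70% | 0.5 | 21.1% v 23.5% | 2.5 | 7.5% |
| 85% / 75% | 0 | 23.5% v 26.7% | 3.1 | 8.6% |
| 85% / 75% | 0.5 | 21.6% v 22.9% | 1.2 | 5.6% |
| 80% / 80% | 0.5 | 22.2% v 22.2% | 0 | about 5% |

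Example: 0.20/(0.90 + 0.10 × 0.5) = 21.1% and 0.20/(0.70 + 0.30 × 0.5) = 23.5%.

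**5. Would counting unobserved men as no event cure it?** Not in general. For 90%/70% with k = 0.5 it gives 0.90 × 21.05 = 18.9% against 0.70 × 23.53 = 16.5%, which is the same 2.5 points with the sign reversed. With k = 1, finishers-only is unbiased, while the no-event rule gives 18% against 14%. The rule is unbiased under unequal finishing only if unobserved men never conceive.

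**The case against.** A reader might infer that follow-up starts only on completion, and that the 20% therefore cannot be scored. The protocol does not support that.

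- The study process, Table 1 and the abstract give a calendar window by phone that is open to every randomised man. No sentence says the calls stop.
- Finishing 90 days can be read as the end of the 90-day period. That reading is plausible: a man with 63 to 89 days of intake meets the compliance threshold, yet literally has not finished 90 days.
- The data analysis section keeps men below 70% in the intention-to-treat analysis, which suggests that their outcomes are to be sought.
- How a missing yes/no outcome is valued is commonly left to a statistical analysis plan, and its absence from an article is no finding by itself.
- The larger type I error figures need unequal finishing between arms, which nothing in the protocol predicts.

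All of this stands, and it limits the point to a contradiction. It does not remove it. The calendar window is too short for most births. The low-compliance rule speaks of leaving the study. The 2-year follow-up of assisted-reproduction outcomes carries no completion condition, whereas the one for the primary outcomes does. Staff should not have to choose between these readings.

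**Conclusion.** The point holds as an inconsistency that should be corrected. Follow-up of early stoppers for conception and live birth is undefined, and the passages conflict on its start, length and coverage. On the literal reading, outcomes of up to about 57 of 286 men may not be collected, and the full analysis set could become a finishers-only comparison. That number is an upper bound under the pooled 20% allowance.

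The bias depends wholly on assumed inputs. It is 1.2 to 6.3 points in the unequal-finishing cases tried. It is nil under no effect when finishing, and the relation of non-finishers to finishers, are the same in both arms. With a true effect, balanced finishing at 80% and k = 0.5, the finishers-only difference is the all-randomised difference divided by 0.9, a modest overstatement. The type I error of about 20% is a worst case that also needs non-finishers never to conceive; it is not an expectation.

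**What to change.** 1. Reconcile the outcome section, the study process and Table 1 into one follow-up for natural conception, pregnancy outcome and live birth. Count it from randomisation, at a fixed length, for every randomised man whatever his intake, and make it long enough to observe live birth. The length should also fit the stated dates: from the anticipated end of recruitment (31/01/2020) to the anticipated end of study (31/01/2022) is 24 months, so a clock running to about month 27 would overrun for the last men recruited.
2. State in the study process that compliance below 70% affects only membership of the per-protocol set and does not end phone follow-up.
3. In the data analysis section, keep the full analysis set of all randomised men as the main analysis of these outcomes. Add a tipping-point analysis that varies, by arm, the assumed rate in men who cannot be reached. Do not fix no event as the single scoring rule, for the reason in step 5 of the working.

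The cost is a wording amendment, extra phone calls to men who stopped early and one sensitivity table.
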